## Abstract

**Background:**

Long COVID-19 is a medical condition associated with persistent physical, cognitive, and emotional symptoms. Despite its significant impact, there are still few psychological interventions—especially with transdiagnostic approaches— that have been rigorously tested in this population. The aim of the present protocol is to describe a randomized controlled trial to examine the effectiveness and acceptability of the online, group-delivered Unified Protocol (UP) for improving emotional, and cognitive outcomes in adults with long COVID-19. We expect greater improvements in emotional and cognitive outcomes for the UP group compared to controls. Additionally, exploratory analyses will assess changes in neurocognitive performance and hair cortisol/cortisone levels as potential correlates of treatment response.

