With all this information in mind, the primary aim of this RCT is to assess the effectiveness and acceptability of the UP delivered in an online group format for treating emotional disorders in long COVID-19 patients. We hypothesize that participants in the experimental group will show improvements in psychological and cognitive outcomes. Specifically, we expect that at post-treatment participants in the experimental group will exhibit reductions in depressive and anxiety symptoms, memory failures, dimensions of emotional disorders (neuroticism, depressed mood, somatic anxiety, arousal activation, social anxiety, intrusive cognitions, traumatic re-experiencing and avoidance), difficulties in emotion regulation and perceived stress. In addition, we anticipate increases in quality of life, distress tolerance and positive temperament scores. We expect these improvements to be maintained at follow-up assessments conducted 3, 6 and 12 months after the intervention. We further hypothesize that participants in the experimental group will show greater improvements in psychological and cognitive outcomes compared to those in the control group. Additionally, the study will examine participant acceptability and satisfaction with the UP intervention and the online group format of delivery, with expectations of high satisfaction and adherence rates.

The secondary aim of this study is to explore the evolution of neurological, cognitive and physiological outcomes in a sample of long COVID-19 patients. Longitudinal changes in cognitive impairments (i.e., visuospatial skills, memory, working memory, attention, concentration, language, executive functions, orientation and verbal short-term memory), cortisol and cortisone levels will be measured in the experimental group to investigate potential neurological and physiological correlates of the UP intervention. To the best of our knowledge, no studies have explored the usefulness of the UP in reducing cognitive impairments or cortisol/cortisone levels in long COVID-19 patients. Consequently, this aspect of the study is exploratory in nature and no formal hypotheses are proposed.

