### Data analysis

First, descriptive statistics of clinical psychological diagnosis, sociodemographic, and long COVID-19 symptoms will be explored to characterize the sample at baseline. Means and standard deviations for psychological measures (i.e., ODSIS, OASIS, etc.) at pre-treatment will also be calculated to provide a baseline description of our sample.

Second, the main effect of time, group and time x group interaction will be analyzed. Several linear mixed-effects models will be employed for each dependent variable to be analyzed (i.e., primary outcomes such as anxiety and depressive symptoms; secondary outcomes such as memory failures, emotional regulation difficulties, etc.). For each of these models, Time (within-subject variable; T1 vs. T2 vs. T3 vs. T4 vs. T5) and Experimental Group (between-subject variable; Experimental vs. Waitlist) will be included as fixed effects. Random slopes for participants will also be considered and included as random effects in the model. The models will have the following structure: [Dependent Variable ~ Time × Experimental Group + (1|Participant)].

In participants from the experimental group, descriptive analyses will also be conducted to assess their neuropsychological and cognitive status, as well as stress levels (hair cortisol and cortisone), prior to starting the intervention. Repeated measures ANOVAs with time as the within-subject factor will be performed to determine whether changes occur in these variables over time (i.e., after the intervention and at 3 and 12-months follow up). Exploratory correlational analyses will be conducted to examine associations between hormonal levels and other dependent variables. Subsequently, multiple linear regression analyses will be performed to determine which hormonal variables significantly predict subjective cognitive complaints, objective cognitive performance, and emotional variables, while controlling for relevant covariates (e.g., age and educational level).

Satisfaction with the intervention will be summarized using means and standard deviations derived from the satisfaction questionnaire. Additionally, adherence to the intervention will be calculated as the proportion of attended sessions relative to those scheduled.

Analyses will be conducted using the lme4 package (version lme4_1.1–13; [46]) in R statistical software (version 4.1.0; [47]) and SPSS v25.0 [48].

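### The abstract asks whether hair-hormone change goes with treatment response, but the named analyses relate hormone levels to outcome variables, so a stable trait association can be mistaken for a link with response

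*Protocol article*

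**What the plan says.** The abstract (Background) sets the question: "exploratory analyses will assess changes in neurocognitive performance and hair cortisol/cortisone levels as potential correlates of treatment response". The Introduction states the secondary aim as exploring how these measures evolve. Longitudinal changes in cognition, cortisol and cortisone are to be "measured in the experimental group to investigate potential neurological and physiological correlates of the UP intervention". It adds that "this aspect of the study is exploratory in nature and no formal hypotheses are proposed".

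The Data analysis section names three analyses that involve the hormones:

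1. Repeated measures ANOVA in the experimental group, with time as the within-subject factor.
2. Correlations: "Exploratory correlational analyses will be conducted to examine associations between hormonal levels and other dependent variables".
3. Regressions: "multiple linear regression analyses will be performed to determine which hormonal variables significantly predict subjective cognitive complaints, objective cognitive performance, and emotional variables". Age and educational level are given as examples of covariates.

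Earlier in the same section, dependent variable is the term for the outcome scores entered in the mixed models, such as anxiety, depressive symptoms and memory failures. The abstract's summary of the analyses likewise speaks only of associations between cortisol and the psychological or cognitive measures.

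Under Procedures, hair is taken before the programme and again at 3 and 12 months. Questionnaires are completed at the same stages.

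**The concern.** A correlate of response is a quantity whose change goes with improvement: the people whose cortisol moves are the people who get better. None of the three named analyses addresses that.

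The ANOVA shows whether the mean hormone level moves. It does not show whether hormone and symptoms move together within people. The correlations and regressions ask whether people with higher hormone levels have worse or better scores. Neither a change score nor a baseline value of the outcome or hormone is named.

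Two errors become possible. If people with high cortisol simply have worse symptoms throughout, the level correlation is significant and can be misread as a link with response. If hormone and symptom changes really go together but stable differences between people are unrelated, those differences dilute the level correlation and the link is likely to be missed.

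**Working it through.** The plan gives no figure for this analysis, so there is none to reproduce. The size of the problem is shown under stated assumptions.

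**Inputs**
- From the protocol: 45 per arm and 20% dropout, so 45 × 0.8 = 36 experimental-group participants; alpha 0.05.
- Assumed: hormone and outcome are each a stable trait plus an independent occasion part. The stable share s of the variance is 0.70, with 0.50 as a sensitivity value. Level correlations are 0.2, 0.3 and 0.4, and the change correlation under the alternative is 0.5.

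**Why levels and changes can disagree.** Write hormone H_t = T_H + e_t and outcome Y_t = T_Y + u_t.
- The level correlation is s × corr(T_H, T_Y) + (1 − s) × corr(e, u).
- In H_2 − H_1 and Y_2 − Y_1 the traits cancel, so the change correlation is corr(e, u) alone.

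**Approximate rejection rate.** With z = atanh(r) × √(n − 3), the rate is P(Z > 1.96 − z) + P(Z < −1.96 − z). For n = 36, √33 = 5.745.

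*Changes unrelated, so corr(e, u) = 0*

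| Level r | Trait r (r/0.7) | z | Level test | Simulated level test | Change-change test |
|---|---|---|---|---|---|
| 0.2 | 0.29 | 0.2027 × 5.745 = 1.165 | 21% | 21-22% | about 5% |
| 0.3 | 0.43 | 0.3095 × 5.745 = 1.778 | 43% | 43-44% | about 5% |
| 0.4 | 0.57 | 0.4236 × 5.745 = 2.434 | 68% | 68-71% | about 5% |

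The simulations used 4,000 data sets per setting. A separate run with 60% stable variance and trait correlations of 0.3, 0.5 and 0.7 gave about 19%, 43% and 74% for the level test at n = 36, and about 22%, 52% and 84% at n = 45. The change-change test rejected in 5-6% at both sizes.

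*Changes correlate 0.5, traits unrelated*
- At 70% stable, level r = 0.3 × 0.5 = 0.15 and z = 0.868, so the level test has 14% power (simulated 13-15%).
- At 50% stable, level r = 0.5 × 0.5 = 0.25 and z = 1.467, so it has 31% power (simulated 32%).
- For the change-change test, r = 0.5 and z = 3.156, so it has 88% power (simulated 89%).

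**Would a baseline-adjusted change regression do instead?** Regressing outcome change on hormone change, adjusted for baseline hormone and baseline outcome, gives the same hormone coefficient as regressing follow-up outcome on follow-up hormone given both baselines. Each baseline is a noisy measure of its trait, so part of the trait association remains. Take level r = 0.4 with changes unrelated.
- The partial correlation is 0.087 at 70% stable and 0.170 at 50% stable.
- With z = atanh(r) × √(36 − 3 − 2), the rejection rates are 8% and 16%. Simulation gave 7-8% and 16-17%.
- Power when changes correlate 0.5 is about 78% and 74%, below the 89% of the plain change-change correlation.

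**The case against.** The strongest reply is that the wording about response stands only in the abstract. The Introduction and Discussion speak of exploring evolution over time, and the ANOVA meets that aim. The correlations are described modestly as associations, and the Introduction disclaims formal hypotheses. Rewording one phrase would then cure the mismatch. Part of this stands. It limits the severity, and no null or alternative hypothesis is stated that the analysis could be said to violate. It does not remove the mismatch: the abstract names treatment response, the Introduction says "to investigate potential neurological and physiological correlates of the UP intervention", and no named analysis serves either phrase at the level of the person.

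A second reply is that the plan does not rule out change scores. The regression refers to hormonal variables, the covariates are only examples, and no time points are fixed. That is right as far as it goes. The correlation sentence does name levels, however, so this is a choice of quantity and not only detail left out of an article.

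A reader might infer that the trial will report level associations as evidence about response. The documents do not say how the results will be read, so only the risk of misreading is supported.

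Third, the percentages depend on assumed stability and correlations. The 89% also presumes no measurement error beyond the modelled occasion variance. The number analysed may exceed 36, because waiting-list participants later follow the experimental-group procedures. In the 60%-stable run at n = 90, the level test was significant in 40-99% of trials with unrelated changes.

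**Conclusion.** The point holds as a mismatch between a stated aim and the named analyses. The abstract asks about hormone change and response, while the analyses cover mean change and associations with hormone levels. Under the trait-plus-state assumptions with 36 participants and 70% stable variance, a stable association alone makes the level test significant in about 22-70% of trials for level correlations of 0.2 to 0.4. The same test finds a real change correlation of 0.5 in only about 13-15% when the stable parts are unrelated. These rates illustrate direction and order of size; they are not forecasts for this trial.

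Severity is minor to moderate. The work is exploratory, is done within the experimental group and carries no formal hypothesis. The primary outcomes and the comparison between groups are untouched.

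**What to change.** In the Data analysis section:

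- Add an exploratory correlation of within-person hormone change with outcome change over the same interval, from pre-treatment to 3 months and from pre-treatment to 12 months. A mixed model that separates within-person from between-person hormone effects would serve equally.
- Where regression is used, keep age and educational level as covariates.
- Do not make the baseline-adjusted change regression the main version, because it removes the stable trait association only in part.
- Keep the level correlations, state their time points, and label them as cross-sectional associations that do not bear on treatment response.

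The cost is wording only. The hair samples and questionnaires needed are already scheduled, and analysis is to follow the end of data collection. The downside is that only participants with paired hair samples contribute, so fewer people enter than in a correlation at baseline.

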## Discussion

The present study protocol describes a RCT exploring the efficacy of a transdiagnostic psychological intervention, the UP, in reducing the emotional and cognitive burden of long COVID-19 compared with a waiting list control group. The experimental group receiving the UP is expected to obtain better results in the psychological and cognitive outcomes after the intervention. Previous studies have indicated that long COVID-19 patients experience both emotional and cognitive complaints [4]. Thus, the primary and secondary outcomes of our study include measures of depression, anxiety, emotional disorders' dimensions, emotion regulation difficulties, quality of life, distress tolerance and perceived stress but also indicators of memory failures. Also importantly, in this study it is proposed a secondary objective to explore the evolution of neurological, cognitive and physiological outcomes before and after the application of the UP. Potential implications for clinical practice and research as well as innovations derived from our study are described below.

The UP has demonstrated robust efficacy in reducing anxiety and depressive symptoms in diverse clinical populations [16,17] also in adults suffering chronic medical conditions [18]. However, previous studies have not explored the potential use of the UP to address cognitive impairments. In this regard, in the systematic review by Osma et al. [18], which focuses on medical health conditions, it is observed that none of the studies applying the UP have incorporated neurocognitive assessments or biological markers of stress as an outcome. To the best of our knowledge, only one ongoing study that will deliver the UP in cancer survivors includes cognitive functioning in their assessment protocol [49], but it does not assess physiological correlates such as cortisol or cortisone levels. This gap is particularly relevant in the context of long COVID-19, where anxiety and depressive symptoms have been linked to dysregulation of stress-response systems, especially the hypothalamic–pituitary–adrenal (HPA) axis and alterations in cortisol regulation (for a review, see Narayanan et al. [50]). In general, sustained dysregulation of the HPA axis has been proposed to contribute to functional alterations in brain regions involved in cognitive functioning, including the hippocampus and prefrontal cortex [51]. As an innovative element, the present study proposes a comprehensive evaluation of the UP in adults with long COVID-19, incorporating not only traditional emotional outcomes but also cognitive performance measures (e.g., memory, attention, concentration, executive functions). In addition, hair samples will be collected to assess objective changes in stress levels through cortisol/cortisone measurements. This multifaceted approach represents a novel extension of UP research, addressing both psychological and physiological dimensions of long COVID-19 conditions, and allowing for a better understanding of the broader effects of transdiagnostic interventions in people suffering chronic medical conditions.

Transdiagnostic psychological interventions to improve emotion regulation skills may play a fundamental role in individuals suffering long COVID-19, with the potential to enhance clinical practice by providing clinicians with effective tools to address the emotional and functional challenges faced by this population. Long COVID-19 patients usually experience physical and emotional symptoms that may interfere with their personal goals and daily activities [52]. The UP may help to address this issue because it trains in core emotional regulation skills. Previous studies have revealed that the implementation of these skills in their daily lives may have the potential to reduce not only anxiety and depressive symptoms but also to help patients to tolerate the discomfort generated by unpleasant emotions [53]. It seems that by learning to tolerate distress and engage in goal-oriented behaviors despite physical and emotional challenges, participants may slowly recover a sense of normality. This idea is supported by preliminary findings in long COVID-19 patients, where most therapeutic objectives were achieved over the course of an UP-based intervention [29].

The provision of the psychological intervention in an online group format constitutes also an innovative and cost-effective approach that will also help to overcome practical and clinical challenges found in long COVID-19 patients. Previous studies have indicated that long COVID-19 patients often report fatigue, muscle paint, general pain and joint pain [4] which may impede travelling to onsite healthcare centers to receive in-person attendance. Thus, online sessions will increase accessibility to psychological care in long COVID-19 populations. As for the group format of delivery it may facilitate peer support and shared learning experiences in health conditions [54]. On the other hand, many individuals with long COVID-19 often report feelings of loneliness, stigmatization and discrimination [55–58] and the group format may provide an opportunity to normalize and validate symptoms and to reduce social isolation. In fact, a recent systematic review indicated that people with long COVID-19 frequently use social media forums and online groups to connect with peers who have similar experiences [59]. Also importantly, the program has been designed considering the cognitive and physical limitations of long COVID-19 individuals, including scheduled breaks to help them to participate fully with the sessions. We expect that these patient-focused adaptations will help to facilitate engagement throughout the program, which should in turn contribute to high levels of satisfaction with the intervention. Taken together, these features not only improve accessibility and engagement but also have important clinical implications, as they provide a patient-centered model of psychological care that can be readily implemented in healthcare settings to address the emotional and social needs of long COVID-19 patients.

Despite the results of this study may have important clinical implications, we need to also acknowledge certain limitations. First, participants and researchers cannot be blinded to the intervention assignment, which may introduce expectancy effects. To minimize this potential bias, online assessments will be conducted so that the researchers are not involved in evaluating the efficacy of the intervention. Second, although sample size has been estimated to be sufficient to detect moderate effects, it may limit generalizability to broader populations or to patients with higher or lower long COVID-19 severities. Third, digital literacy of potential participants may interfere or even impede their participation in the study. For instance, participants may present difficulties to engage with the online platform to respond to the psychological assessments or they may find difficulties to engage in the online sessions through videocalls. These potential technology-related challenges will be partially mitigated by the support of the therapist who will explain the procedures for completing the assessment protocol and engaging in the online sessions. Additionally, satisfaction questions regarding the online format will also be included to capture participants’ opinion about the intervention and to evaluate whether these issues have been adequately addressed. Related with participants’ interest in this study, it is possible that some participants may show reluctance when asked to provide a hair sample. To minimize this potential concern, the research team will explain to participants that the hair sample consists of collecting only 5–6 strands from the back of the head and it will not affect their physical appearance. Finally, another potential limitation is that, for ethical reasons, participants in the control group will be offered the opportunity to join in the experimental group after completing the post-treatment assessment. Consequently, only the experimental group will be available for follow-up assessments, and comparisons between groups will be limited to the post-treatment time point.

In conclusion, this trial seeks to address an important gap in mental health care for long COVID-19 populations. By implementing a flexible, group-based, and online transdiagnostic intervention, the study has the potential to improve emotional well-being, enhance emotion regulation skills, reduce cognitive complaints and provide insights for both clinical practice and public health strategies. If our results proved the effectiveness of the UP delivered in an online group format it could offer a valuable, scalable, accessible, and evidence-based psychological intervention to address the psychological needs of long COVID-19 patients.
